## Abstract

**Background:** Assessing the real-world safety of preventive products against respiratory syncytial virus (RSV) in pregnant women holds significant public health implications, especially as vaccination programs become more widespread. This generic protocol describes a post-authorisation safety study (PASS) to evaluate the safety of RSV vaccination in pregnant women using a target trial emulation framework. **Methods:** This generic protocol, adapted from an ongoing PASS, is designed using the target trial emulation framework to evaluate the safety of an RSV vaccine in pregnant women. Emulating target trial conditions have the ability to minimise confounding and bias. In this pragmatic real-world observational study, RSV-vaccinated pregnant women are matched (1:N) with unexposed women based on gestational age, calendar time, maternal age, immunocompromised status, and high-risk pregnancy. Key adverse outcomes include preterm birth, stillbirth, hypertensive disorders of pregnancy, Guillain-Barré Syndrome (GBS), low birth weight (LBW), and small for gestational age (SGA). Future studies may add additional outcomes per vaccine risk profile and Global Alignment of Immunization safety Assessment (GAIA) recommendations. Distinguishing outcomes measured during pregnancy from those assessed at or after birth is crucial for analysis and interpretation. **Conclusions:** This protocol offers a structured approach to evaluating the safety of RSV vaccines in pregnant women. It aims to guide researchers in designing studies and should be adapted to specific settings and data availability.

## 1. Introduction

Respiratory syncytial virus (RSV) is a major cause of lower respiratory tract infections (LRTIs) in young children. In 2019 alone, RSV was responsible for 33 million LRTIs globally, leading to 3.6 million hospitalisations and around 100,000 deaths [1]. Notably, about half of the global burden of RSV falls upon infants under the age of 6 months, with a significant number occurring during the neonatal period [1]. Given the substantial impact of RSV, introducing an RSV vaccine for maternal immunisation during pregnancy may offer promise in reducing the burden of RSV-associated illness in infants [2]. The mechanism underlying maternal immunisation involves transferring antibodies across the placenta to protect the infant during its vulnerable neonatal period and beyond [3].

The development of RSV vaccines is progressing swiftly, with multiple candidate vaccines advancing through phases 2 and 3 of development [4]. In 2023, the first maternal RSV vaccine was approved by the European Medicines Agency (EMA), the Food and Drug Administration (FDA) and the Medicines and Healthcare products Regulatory Agency (MHRA) [5,6,7]. These approvals in pregnant women in the EU, US and UK are supported by evidence from a global randomized, double-blinded, and placebo-controlled trial (MATISSE). This trial assessed the vaccine’s efficacy, safety, and immunogenicity against RSV-related medically attended LRTI in infants born to vaccinated healthy women during weeks 24 to 36 of gestation. The study enrolled 7358 pregnant women, receiving either the RSV vaccine or placebo. At the time of analysis, 5654 infants (79%) completed 6-month follow-up after birth, with follow-up ongoing for a total of 24 months [8].

Immunocompromised pregnant women and those with high-risk pregnancies were excluded from the trial [8]. As a result, there is a need for further post-authorisation safety studies (PASS) to understand the vaccine’s safety profile in these populations. Additionally, Guillain-Barré Syndrome (GBS), a rare neurological disorder, has been reported as an adverse event in the clinical trial of the approved vaccine in older adults [9]. Although GBS has not been reported in clinical trials in pregnant women, we identify it as a safety event of interest.

In the MATISSE trial, there was no evidence of a difference in the percentage of preterm births between the vaccine and placebo groups overall. However, analyses stratified by income level revealed a statistically significant difference in upper-middle-income countries [10]. Of note, another trial of a candidate maternal RSV vaccine of a similar type stopped early due to a higher risk of preterm birth in the vaccine group [11]. As the first vaccine to be approved for maternal indication and given this potential uncertainty about preterm birth, the regulatory agencies each approved the vaccine to be used at different gestational ages [12]. The EMA decided that the vaccine could be administered beginning at 24 weeks of gestation. The FDA approved vaccination of pregnant women at 32 through 36 weeks of gestation, while the MHRA has recommended that the vaccine may be given in the third trimester of pregnancy (weeks 28 to 36 of gestation) [13].

In light of the importance of addressing gaps in safety data, a protocol for a PASS to assess the safety of this RSV vaccine in pregnant women and their offspring in real-world settings was developed as an additional pharmacovigilance activity outlined in the EU and UK-approved risk management plans and as a post-marketing requirement to the FDA [14,15]. This manuscript provides a generic framework of the PASS protocol to assist researchers in the preparation of their own protocols during the post-marketing phase in the coming years.

## 2. Objectives

The primary objective of a PASS on maternal RSV immunisation study is to estimate the occurrence of adverse maternal, pregnancy and birth outcomes in women who receive the vaccine during pregnancy (and their offspring), compared with a matched comparator group of pregnant women who do not receive the RSV vaccine during pregnancy (and their offspring). The secondary objectives may include assessing the occurrence of these adverse outcomes in immunocompromised or high-risk pregnant women who receive the RSV vaccine compared to those who do not, as these groups were not studied in clinical trials. Due to variations in timing of authorised administration, another objective may be to estimate the occurrence of adverse outcomes by gestational week of vaccination to better understand possible effect modification by week of gestation.

## 3. Methods

### 3.1. Study Design

We recommend an observational retrospective comparative cohort study of pregnant women who receive the RSV vaccine compared to an unexposed pregnant comparator group (or an active comparator group when there is one). To assess whether the RSV vaccine increases the risk of any adverse outcome in pregnancy or offspring, we propose designing the study to emulate a hypothetical pragmatic randomised trial (Table 1) [16]. This trial would assess the safety of administering one dose of the RSV vaccine between 24 and 36 weeks of gestation in pregnant women compared to pregnant women who do not receive an RSV vaccine (Figure 1A). As we cannot truly randomise participants, we need to emulate this feature by carefully addressing confounding biases through various techniques such as matching and careful assessment of inclusion criteria. These techniques also have the potential to address both selection bias and immortal time bias. Time zero, designated as day 0, marks the point at which the eligibility criteria are fulfilled, and the RSV vaccine is administered to the pregnant woman.

At Time zero, exposed participants should be matched to unexposed pregnant participants eligible to receive the vaccine (1:N ratio) based on (Figure 1B):Gestational age (same week of gestation) to account for timing of vaccination in pregnancy and the risk of preterm birthCalendar time (same week) because of RSV seasonality and probability of exposureMaternal age (year of birth) because of the association with adverse pregnancy outcomesImmunocompromised status because of the association with adverse maternal outcomesHigh-risk pregnancy because of the association with adverse pregnancy outcomes

Additional characteristics may be added that would confound the association.

A primary analytical concern is the gestational age at Time zero, which directly impacts the risk of preterm birth. Therefore, it is imperative to ensure a robust match on gestational age, and in fact, we recommend emulating a series of separate target trials for different gestational ages at vaccination, i.e., 24, 25, 26, …, or 36 weeks to study effect modification [17]. Follow-up of the exposed and unexposed (or active comparator) pregnant women should start on day 1, and end at the earliest of N months after birth depending on the outcome being measured, maternal death, disenrollment or migration, end of data availability in the data source, treatment crossover, or occurrence of a given outcome. Treatment crossover, or protocol violation, occurs when previously unexposed pregnant women in the matched comparator cohort receive vaccination with an RSV vaccine during pregnancy. To uphold statistical power, unexposed pregnant women within the matched comparator cohort ought to be censored upon treatment violation, while exposed pregnant women should remain uncensored (see Section 3.10). When unvaccinated pregnant women receive an RSV vaccine, they become eligible for inclusion in the vaccinated cohort (Figure 1C). Follow-up of offspring to assess birth outcomes will depend on the risk window for measuring the outcome and will end at the earliest of N months of age, neonatal death, disenrollment or migration, end of data availability in the data source, or occurrence of a given outcome.

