### 3.6. Exposure

The exposure of interest is RSV vaccination during pregnancy. The vaccine data could be obtained from pharmacy dispensing records, general practice records, immunisation registers, vaccination records, medical records or other databanks. We will consider a single administration of one dose between 24–36 weeks of gestation. An woman is considered exposed from the date of vaccination until the end of pregnancy for all pregnancy and birth outcomes.

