## Figures and Tables

**Figure 1 vaccines-13-00272-f001:**
[figure not shown]
Study design. * Matching should be on gestational age (same week of gestation), calendar time (same week) and maternal age. Additional characteristics may be added.

**Table 1 vaccines-13-00272-t001:** A summary of the protocol of the MATISSE trial and emulation of this target trial to estimate the effect of RSV vaccination during pregnancy.

Protocol Component	Target Trial	Emulation
Eligibility criteria	Healthy women, 49 years of age or younger, at 24 through 36 weeks’ gestation on the day of planned injection, with an uncomplicated, singleton pregnancy and no known increased risk of pregnancy complications.	We maintain the 24 through 36 weeks gestation requirement but do not apply strict age restrictions or restrictions regarding pregnancy complications. Instead, we stratify the analysis based on high-risk pregnancies.
Treatment strategies	(1) A single intramuscular injection of 120 μg of RSVpreF vaccine (60 μg each of RSV A and RSV B antigens) (2) Placebo	(1) RSV vaccination (2) No RSV vaccination
Assignment procedures	Women were randomly assigned in a 1:1 ratio to receive either the RSV vaccine or a placebo, and they were not aware of the strategy to which they had been assigned.	Exposed women will be matched to unexposed women (1:N ratio) based on: Gestational age (same week of gestation) Calendar time (same week) Maternal age (year of birth) Immunocompromised status High-risk pregnancy

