**Pregnancy outcomes**			
Preterm birth [23]	Preterm birth is defined by the WHO as babies born alive before 37 weeks of pregnancy are completed. It is further subcategorised based on gestational age: Extremely preterm (less than 28 weeks) Very preterm (28 to less than 32 weeks) Moderate to late preterm (32 to 37 weeks)	Pregnancies ending with live births	From time of vaccination to before week 37 of gestation (36 weeks and 6/7 days)
Time between vaccination and birth	Time between vaccination and birth in days.	Pregnancies ending with live and non-live births	From time of vaccination to time of birth
Stillbirth [24]	Stillbirth is defined by the WHO as the death of a foetus that has reached a birth weight of 500 g, or if birth weight is unavailable, gestational age of 22 weeks or crown-to-heel length of 25 cm. It is further subcategorised based on gestational age: Late foetal deaths (greater than 1000 g or after 28 weeks) Early foetal deaths (500–1000 g or 22–28 weeks)	Pregnancies ending with live and non-live births	From time of vaccination to end of pregnancy

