**Birth outcomes**			
Low birth weight (LBW) [28]	Low birth weight is defined by the WHO as a weight at birth of less than 2500 g, regardless of gestational age.	Pregnancies ending with live births	From birth until one month after birth
Small for gestational age (SGA) [29]	Small for gestational age is defined by the WHO as a birth weight below the 10th percentile for gestational age and sex. SGA can be caused by placental dysfunction, referred to as foetal growth restriction (FGR), or it can be due to a constitutionally small foetus without any pathological causes. Other possible causes include congenital malformations or infections.	Pregnancies ending with live births	From birth until one month after birth

**Table 3 vaccines-13-00272-t003:** Covariates of interest.

Covariate	Definition
Gestational age at time of vaccination	Gestational age at time of vaccination is defined as the time between the last menstrual period (LMP) and the date of vaccination, measured in weeks.
Calendar time at time of vaccination	Calendar time at the time of vaccination is defined as the specific calendar date of the vaccination, expressed in weeks (e.g., week 48 of the year 2024 or week 12 of the year 2025).
Maternal age	Maternal age at time of vaccination is defined as the age of the pregnant person at the date of vaccination. This age is determined by subtracting the individual’s date of birth from the date of vaccination.

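### Same-week matching leaves up to 6 days' difference in gestational age at Time zero; this matters for preterm birth mainly in the week 34–36 trials, and balance checks in weeks cannot show it

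*Protocol article*

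**What the plan says.** Section 3.1 (Study Design) lists the matching factors, the first being "Gestational age (same week of gestation) to account for timing of vaccination in pregnancy". Table 1 repeats the same-week rule in its emulation column. Table 3 defines gestational age at vaccination as "the time between the last menstrual period (LMP) and the date of vaccination, measured in weeks".

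Section 3.1 treats this variable as the main analytical concern because it directly affects preterm risk, and states that "it is imperative to ensure a robust match on gestational age". Its further safeguard is also weekly: "we recommend emulating a series of separate target trials for different gestational ages at vaccination", one for each week from 24 to 36.

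Three other provisions set the length of the preterm risk window:
- Start (Section 3.1): "Follow-up of the exposed and unexposed (or active comparator) pregnant women should start on day 1".
- End (Table 2): "From time of vaccination to before week 37 of gestation (36 weeks and 6/7 days", closing parenthesis omitted.
- Eligible vaccinations (Section 3.6): "We will consider a single administration of one dose between 24–36 weeks of gestation".

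Sections 3.10.1 and 3.10.2 check comparability with standardised differences, use multivariable generalised linear models, and allow propensity-score methods where imbalance remains. The Discussion names preterm birth as the primary outcome measure. Time from vaccination to birth, in days, is offered as the more powerful companion outcome.

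**The concern.** The article's argument for matching tightly is that a woman vaccinated late cannot deliver before her vaccination date. The Discussion illustrates this with vaccination at 35 weeks. The same argument applies inside a week: a woman indexed on the last day of week 35 has about half the preterm window of one indexed on its first day, yet the two count as matched. In week 36 the window can shrink to nothing.

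Matching on the same calendar week does not close the gap, because the start of pregnancy can still differ by up to 6 days. The balance check does not expose it either. Once women are matched on week, the standardised difference of a variable held in weeks is zero by construction, so the trigger for further adjustment cannot fire.

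At stake is the primary outcome in the latest weekly trials, and time from vaccination to birth in all of them. Because the article is a template, studies that adopt its definitions would inherit the weekly unit.

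**Working it through.** **The plan's own figure.** The only preterm figure in the article is the study size in Section 3.9, about 1200 for a risk ratio of 1.5. Taking 6.0% versus 9.0%, two-sided 5% alpha, 80% power and 1:1 allocation gives 1209 per group. That the 6.0% is the preterm rate and that 1200 is per group at 1:1 are assumptions. The point below does not depend on this figure.

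**Inputs.** Same-week match (Section 3.1, Table 1); gestational age in weeks (Table 3); follow-up from day 1 (Section 3.1); window ends at 36w6d (Table 2); weekly trials 24 to 36 (Section 3.1). I take week 36 to mean 36w0d to 36w6d.

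**Days at risk.** For a woman indexed in week w, day d (0 to 6): days = (36 − w) × 7 + 6 − d. At 36w0d this is 6; at 36w6d it is 0.

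**Spurious risk ratio with no vaccine effect.** The article gives no within-week offset, so one is assumed: vaccinated women indexed on average 1 day earlier. With a flat daily hazard and a rare event, the ratio of risks is about the ratio of days at risk. Column A puts the comparator at mid-week (d = 3). Column B puts the groups half a day either side of mid-week. Column C replaces the flat hazard by one rising 20% to 40% per week, scaled to a 6% total from week 24, comparing day 2 with day 3.

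| Week | Days at risk, d = 0 to 6 | A | B | C |
|---|---|---|---|---|
| 36 | 6 to 0 | 4/3 = 1.33 | 3.5/2.5 = 1.40 | 1.30–1.32 |
| 35 | 13 to 7 | 11/10 = 1.10 | 10.5/9.5 = 1.11 | 1.08–1.09 |
| 34 | 20 to 14 | 18/17 = 1.06 | 17.5/16.5 = 1.06 | 1.04–1.05 |
| 32 | 34 to 28 | 32/31 = 1.03 | 31.5/30.5 = 1.03 | 1.01–1.02 |
| 28 | 62 to 56 | 60/59 = 1.02 | 59.5/58.5 = 1.02 | 1.00–1.01 |
| 24 | 90 to 84 | 88/87 = 1.01 | 87.5/86.5 = 1.01 | 1.00 |

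A 2-day offset in week 36 gives 5/3 = 1.67 (A) or 4/2 = 2.0 (B). If vaccinated women are indexed 1 day later instead, week 36 gives 2/3 = 0.67 (A) or 2.5/3.5 = 0.71 (B), which would hide a harm.

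**Pooled over weeks, equal uptake per week (assumed), flat hazard, 1-day offset.**
- Weeks 32–36: mean mid-week days = (3 + 10 + 17 + 24 + 31)/5 = 17, so 18/17 = 1.06.
- Weeks 24–36: mean mid-week days = 3 + 7 × 6 = 45, so 46/45 = 1.02.

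**Time from vaccination to birth.** Indexing 1 day earlier lengthens this outcome by about 1 day in every weekly trial, whatever the week.

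**No offset.** If index days are uniform within the week in both groups, 1 − 7/49 = 86% of pairs still differ by at least 1 day, with a mean absolute difference of 2.3 days, but the expected risk ratio is 1.00. The index day then adds variance (49 − 1)/12 = 4 days². Against an assumed standard deviation of 10 to 14 days for time to birth, that is 4/100 = 4% to 4/196 = 2% of its variance.

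**The case against.** The strongest reply is that same-week matching combined with weekly trials is a reasonable design, and that scaling a covariate in a regression belongs in the statistical analysis plan, to which Section 3.10 defers. The article also leaves room for a finer variable: Section 3.1 allows extra matching characteristics, and Section 3.10.2 provides for multivariable models and propensity scores. This stands in part, and nothing in the article forbids using days. But the unit is something the article does fix, in Table 3. A weekly unit also disables the balance check that would otherwise prompt the refinement.

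The second reply is that the bias is hypothetical, since it needs a systematic within-week offset and none is documented. This stands in full. Vaccination at booked visits is one conceivable source, but the article says nothing on it.

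Third, day-level dating may be false precision. Section 3.2 asks for the accuracy of pregnancy start dates to be checked, and Section 3.4 foresees algorithms to estimate them. This limits the gain but does not remove it: time to birth and the 36w6d cut-off already call for day-level dates.

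A reader might also infer that gestational age is recorded only in completed weeks, or that the last menstrual period is known to the day. The article says neither. Table 3 gives a unit for an interval between two dates and makes no claim about how exact those dates are.

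**Conclusion.** The point holds as a minor to moderate weakness, mainly for the week 34–36 trials. The day counts follow directly from the article's own rules, and a balance check in weeks cannot detect a within-week imbalance. If both groups are distributed alike within the week, the cost is a small loss of precision for preterm birth and time to birth.

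A spurious preterm effect arises only with a systematic offset, whose size and direction are unknown. For an assumed 1-day offset, flat hazard and no vaccine effect, it is about 1.3–1.4 in week 36, 1.10 in week 35 and 1.06 in week 34, and somewhat less in most weeks if the hazard rises towards 37 weeks. Time to birth would shift by about one day in every weekly trial.

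A reader might take the week 36 ratio as the bias in the primary result. The documents do not support that: with equal uptake by week the same offset gives about 1.06 over weeks 32–36 and 1.02 over weeks 24–36. Nor do they support saying that the preterm comparison is biased as designed; it is exposed to an imbalance that it does not measure.

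**What to change.** Keep the same-week match, so that no matched sets are lost. Then:

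1. In Table 3, define gestational age at Time zero in days, where the data source supports day-level dating, and state which sources do not.
2. Include it as a covariate in the preterm birth and time-to-birth models, which Section 3.10.2 already makes multivariable.
3. Report its standardised difference within each weekly trial, beside the other balance measures.

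The cost is one definition, one model term and one line per balance table, with no new data beyond the dates already needed. The small downside is that where the start of pregnancy is estimated by algorithm, the day-level value carries dating error and the adjustment gains less.

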### 3.5. Recommended In- and Exclusion Criteria

Participants are eligible if they:have an identified start of pregnancy date.are enrolled in the healthcare system for a least 12 months prior to Time zero (date of vaccination).have at least one day of follow-up after Time zero for maternal outcomes and at least 10 months of follow-up after the LMP for birth and pregnancy outcomes.

Participants are excluded if they:are exposed to an RSV vaccine prior to the current pregnancy or before or after the gestational week for which the vaccine is licensed (vaccination in a prior pregnancy is permitted).cannot be linked in the data source to their child (mother-child linkage).

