Follow-up period	For each maternal participant, including her fetus, data on adverse events were collected from the time of informed consent to 1 month after injection, and data on serious adverse events were collected from the time of informed consent through 6 months after delivery. Safety end points in the infant participants included adverse events from birth to 1 month of age. Additional safety end points were serious adverse events and newly diagnosed chronic medical conditions from birth through 12 to 24 months of age. For vaccine efficacy outcomes in infants started at 72 h after birth and continued through 12 to 24 months of age.	Follow-up of the exposed and unexposed (or active comparator) pregnant women should start on the day after eligibility criteria are fulfilled and end at the earliest of N months after birth depending on the outcome being measured, maternal death, disenrollment or migration, end of data availability in the data source, treatment crossover, or occurrence of a given outcome. Follow-up of offspring to assess birth outcomes will depend on the risk window for measuring the outcome and will end at the earliest of N months of age, neonatal death, disenrollment or migration, end of data availability in the data source, or occurrence of a given outcome.
Outcome	Safety: The primary safety end points were reactogenicity and adverse events in the maternal participants and adverse events and newly diagnosed chronic medical conditions in the infants. Efficacy: The two primary efficacy end points were medically attended severe RSV-associated lower respiratory tract illness and medically attended RSV-associated lower respiratory tract illness.	For post-authorisation safety study purposes, the focus is solely on safety, encompassing preterm birth, stillbirth, hypertensive disorders of pregnancy, low birth weight (LBW), small for gestational age (SGA), and Guillain-Barré Syndrome (GBS).
Causal Contrasts of Interest	Per protocol analysis	Observational analog of per-protocol effect
Analysis	Per protocol analysis	Same per-protocol analysis, except for restriction to pregnancies without loss-to-follow up

**Table 2 vaccines-13-00272-t002:** Outcomes of interest.

Outcomes	Clinical Definition	Pregnancies Among Which the Outcome Will be Ascertained	Exposure Risk Window for Outcome

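### Section 3.1 and Table 1 leave day 0 out of follow-up, but Table 2 opens four outcome windows on it, so day-0 deliveries in comparators can count as preterm and pull late-week ratios below 1

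*Protocol article*

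**What the plan says.** Section 3.1 defines Time zero as day 0, the day on which a woman meets the criteria and is vaccinated. Her comparators must be pregnant and eligible for the vaccine at that point. Section 3.1 continues: "Follow-up of the exposed and unexposed (or active comparator) pregnant women should start on day 1". The emulation column of Table 1 agrees: follow-up "should start on the day after eligibility criteria are fulfilled".

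Table 2 gives the preterm birth window as "From time of vaccination to before week 37 of gestation". The windows for stillbirth, hypertensive disorders and GBS also open at vaccination. The document does not say whether the start of follow-up or the Table 2 window prevails.

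On entry, section 3.5 requires that women "have at least one day of follow-up after Time zero for maternal outcomes and at least 10 months of follow-up after the LMP", with the second part applying to birth and pregnancy outcomes. Table 2 lists preterm birth as a pregnancy outcome, ascertained among live births. No rule covers a birth later on day 0.

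**The concern.** Whether a day-0 birth counts depends on which section the analyst follows. Under section 3.1 it precedes follow-up. Under Table 2 and section 3.5 it is inside the window, and the mother qualifies: she can have 10 months of data after her LMP whether or not she delivered on day 0.

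The two cohorts are not alike on that day. A vaccinated woman was still pregnant when injected, and a woman in labour is unlikely to be vaccinated. A comparator has no injection time, so with date-level records her day 0 is a whole calendar day. Counting day-0 births would then give comparators up to one extra day at risk, a small form of the immortal time bias that section 3.1 hopes to address.

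The direction is towards finding the vaccine safe. The effect grows as the window to 37 weeks shortens, so it could look like effect modification by gestational week, which section 2 names as a possible objective. The discussion names preterm birth as the primary outcome, and section 3.1 recommends a separate emulated trial for each week. Because this is a generic protocol for others to adapt, teams could resolve the conflict differently and obtain results that are not comparable.

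**Working it through.** **The plan's own figure.** The plan gives no number for day-0 births. The nearest figure is in section 3.9: about 1200 pregnancies to detect RR 1.5 for preterm birth. With 6.0% v 9.0%, two-sided 5%, 80% power and 1:1 matching:

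n = [1.960 × √(2 × 0.075 × 0.925) + 0.842 × √(0.09 × 0.91 + 0.06 × 0.94)]² / 0.03² = (0.730 + 0.313)² / 0.0009 ≈ 1209 exposed.

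The figure reproduces as the number exposed at 1:1. The point does not rest on it; it only supports using 6% as the preterm risk below.

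**Inputs from the protocol.** Day 0 is the vaccination day. The preterm window ends at 36 weeks and 6 days. The weekly trials run from 24 to 36.

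**Assumptions not in the protocol.**
- Time zero is spread evenly over the seven days of each week.
- Preterm risk from week 24 is 6%, with a daily hazard that is flat, doubles every 3 or every 2 weeks, or rises by weekly steps from 0.08% in weeks 24-27 to 2.3% in week 36.
- Vaccinated women have no day-0 births, or half the comparators' rate.
- There is no true vaccine effect.
- For pooled figures, each gestational week contributes equally.

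**Flat hazard, by hand.** A comparator with Time zero on day d (0 to 6) of week w has 259 − 7w − d days at risk, counting day 0. The mean over d is D = 256 − 7w. Without day 0 it is D − 1, so the null ratio is approximately (D − 1)/D.

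| Time zero in | D | Null ratio, flat hazard | Range over all hazard shapes |
|---|---|---|---|
| Week 24 | 88 | 87/88 = 0.99 | 0.99-1.00 |
| Week 32 | 32 | 31/32 = 0.97 | 0.97-0.99 |
| Week 34 | 18 | 17/18 = 0.94 | 0.94-0.98 |
| Week 35 | 11 | 10/11 = 0.91 | 0.91-0.94 |
| Week 36 | 4 | 3/4 = 0.75 | 0.75-0.76 |
| Weeks 32-36 pooled | 18 | 17/18 = 0.94 | 0.94-0.96 |
| Weeks 24-36 pooled | 46 | 45/46 = 0.98 | 0.98-0.99 |

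The last column comes from day-by-day survival to 36 weeks and 6 days under each hazard shape. In week 36 a true ratio of 1/0.75 = 1.33 would read as 1.0.

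**Half the day-0 births kept among vaccinated women.** The ratio becomes (D − 0.5)/D: 3.5/4 = 0.875 in week 36 (0.88 across the shapes) and 10.5/11 = 0.95 in week 35 (up to 0.97 across the shapes).

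**Both cohorts still pregnant at the end of day 0 and counted from day 1.** The ratio is 1.00 in every week.

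**The case against.** The strongest reply is that the protocol already contains the safeguard. Section 3.1 and Table 1 each start follow-up on day 1 for both cohorts, and nothing gives Table 2 priority. Under that rule a day-0 birth falls before follow-up in both cohorts and there is no bias. This stands, so the bias can only be stated conditionally. A reader might infer that comparators delivering on day 0 are counted as preterm; the document does not say so. It leaves the matter open.

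A reader might also see a conflict with section 3.6, where a woman "is considered exposed from the date of vaccination until the end of pregnancy for all pregnancy and birth outcomes". That sentence defines exposure status, not which events are counted, and is compatible with follow-up from day 1.

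Nor does section 3.10.2 settle the analysis. It assigns risk or rate ratios to events during pregnancy and prevalence ratios to outcomes measurable at birth, without placing preterm birth in either group. A risk or rate over follow-up would drop day-0 births. A proportion among live births would keep them unless entry excludes them. Section 3.9 sizes pregnancy and birth outcomes by prevalence, so the second approach is a natural one.

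The size is also open to challenge. The 0.75 belongs to one of 13 weekly strata and to the assumption least favourable to the plan. Over weeks 24-36 the distortion is 1 to 2%, small beside the smallest planning ratio of 1.5. This stands too.

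Finally, a same-day tie-break is usually left to the analysis plan. That would answer an omission. Here the document gives two different starts and an entry condition that covers only some outcomes, and a later plan would inherit the contradiction.

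**Conclusion.** The inconsistency is real. Follow-up starts on day 1 in section 3.1 and Table 1, four Table 2 windows open on day 0, and the one-day condition in 3.5 does not extend to pregnancy and birth outcomes. As written, a comparator who delivers on day 0 is admissible and can be counted as preterm.

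The resulting bias is conditional. It requires that day-0 births are counted and that vaccinated women have fewer of them than comparators. The second condition is plausible but is not in the document. Under both, the lean below 1 is material in week 36, modest in week 35 and negligible in early weeks and over the full range. The week-36 figure depends little on the hazard shape; the pooled figures also assume equal numbers in each week. The analysis at risk is the late-week trials and any comparison across weeks. The document does not support a claim that the overall preterm ratio would be seriously distorted.

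The change should be made, because it is cheap and the possible error favours a conclusion of safety.

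**What to change.** 1. In section 3.5, state one day-0 rule for both cohorts: for pregnancy and birth outcomes, a woman enters only if she is still pregnant at the end of day 0. Extending the one-day condition would not be enough, because maternal follow-up can continue after birth and a woman who delivers on day 0 can still have a day of follow-up.
2. In Table 2, align the opening of the preterm birth, stillbirth, hypertensive disorder and GBS windows with the day-1 start.
3. List day-0 births and events separately by cohort, so that a same-day event after vaccination remains visible.

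Leave section 3.6 unchanged, as well as the LBW and SGA windows, which run from birth, and the origin of time between vaccination and birth, which is vaccination by definition.

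The cost is a few words in section 3.5 and Table 2, plus one listing. The downside is that the few events later on the vaccination day move from the ratio to the listing.
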